**Date final：2011/02/01**

**version：1.0**

**Protocol summary**

| Ttitle | Phase II study of *Pseudomonas aeruginosa*-mannose-sensitive hemagglutinin(PA-MSHA) in combination with capecitabine for Her-2–negative metastatic breast cancer |
| --- | --- |
| Study site | Fudan university cancer centre |
| Study objectives | To assess the efficacy and safety of PA-MSHA in combination with capecitabine in Her-2 negative metastatic breast cancer. |
| Study design | Phase II, single arm, single center clinical trial. |
| Study population | MBC pretreated with antracycline and taxane. |
| Number of patients | 96 |
| Study regime | PA-MSHA 1 mg was administered subcutaneously every other day and capecitabine1000 mg/m2 orally twice a day for 2 weeks on, 1 week off. |
| Primary endpoint | Progression free survival（PFS） |
| Secondary endpoint | Overall response rate（ORR）、Overall survival（OS）、safety、exploratory endpoints such as immune index. |
| Inclusion criteria | 1) Women aged between 18 and 70 years；  2) Histologically confirmed Her-2–negative MBC；  3) Not suitable for local treatment;  4) Pretreated with antracyclene and taxane；   1. Prior capecitabine-containing therapy was permitted if the disease had responded to the drug previously and progressed at least 4 months after drug discontinuation； 2. ECOG performance status of no more than 2；   7) Adequate organ function；  8) Having the following laboratory values; WBC≥4×109/L；Hb≥90 g/L；plt≥100×109/L；  9) Written informed consent should be obtained before study procedure. |

**I．Introduction**

1. **Treatment status of metastatic breast cancer (MBC)**

Breast cancer is the most common malignant tumor in women. There are about 1 million new breast cancer patients in the world every year, and more than 410 thousands died of it. The incidence of breast cancer also rises fast in recent years in China. In 2000, the age-adjusted prevalence of breast cancer was 19.9/100 thousands in China. And it has become the most common malignant tumor in Chinese women. Though significant progress has been made in the diagnosis and treatment of breast cancer, most of the breast cancer patients still appear recurrence eventually due to the biological behaviors of the cancer as well as the lower early diagnosis rate. Metastatic breast cancer (MBC) has been considered as an incurable disease currently, with the median survival time of only 2-3 years. MBC treatment aims at prolonging the survival time, reducing the symptoms associated with the disease and improving the patient’s quality of life. Therefore, it is particularly important to explore new antitumor drugs and new treatment, reduce the side effect of treatment and improve the patient’s quality of life.

Recent studies have shown that invasive breast cancer can be divided into several basic subtypes with cDNA microarray, including luminal A, luminal B and hormone receptor negative subtype, namely the HER2 positive and basal- like subtypes. In the conventional treatment, the patients were classified according to whether the patients had excessive expression of hormone receptor (estrogen receptors (ER) and/or progesterone receptors (PgR)) and/or human epidermal growth factor receptor-2 (HER-2). For hormone receptor-positive tumors, endocrinotherapy is the common selection due to relatively good response, easy to use and low toxicity. For HER2 positive subtype, Herceptin based therapies were often chosen. For three negative patients or patients with hormone receptor-positive but also with drug resistance against endocrinotherapy, cytotoxic chemotherapy is the standard treatment. Monotherapy and combination treatment are both effective MBC treatments. Combination therapy has improved disease remission rate and time of disease progression, but it has little benefit on survival, and in addition, the toxicity was increased remarkably because of administration of a variety of cytotoxic drugs.

Commonly used chemotherapy drugs in MBC treatments include anthracyclines (e.g., doxorubicin (DXR), epirubicin (EPI)), taxanes (e.g., docetaxel, paclitaxel), alkylating agent (such as cyclophosphamide), capecitabine (Xeloda), vinocrelbine and gemcitabine [1]. Anthracyclines are considered to be one of the most effective treatments for breast cancer, which are usually used in the initial treatment. Taxanes have also been considered a very effective agent for MBC [2]. But as anthracyclines and taxanes gradually widely applied in the adjuvant and neoadjuvant therapy, drug selection for MBC is limited [3].

For patients pretreated with anthracyclines and taxanes, capecitabine can be an important choice, which is also the only drug approved to use in this setting. Patients pretreated with anthracyclines and taxanes have a response rate as high as 28% in monotherapy with capecitabine [4-6]. The drug also has the advantage of oral administration and mild bone marrow suppression. For patients pretreated with anthracyclines and taxanes, other choices include gemcitabine, vinocrelbine, liposomes doxorubicin [7].

In addition, biological treatment has gradually entered into the clinical application of metastatic breast cancer treatment [1]. For HER-2 positive tumor patients, trastuzumab has become the key agent in standard therapy of this subgroup. However, for HER-2 negative breast cancer, there is no standard biological treatment . Bevacizumab, the anti-angiogenesis drug which used to be a hot spot, has come to be questioned in MBC treatment now.

**2. Capecitabine and MBC treatment**

Some clinical studies have evaluated the efficacy of capecitabine used alone or in combination for MBC. Capecitabine combined with docetaxel has been approved for MBC patients pretreated with anthracycline-based chemotherapy [8]. In addition, capecitabine is currently approved as monotherapy for MBC patients pretreated with taxane and anthracycline-based chemotherapy. Capecitabine is administered at the dose of 1250 mg/m2, twice every day, for 2 weeks on and 1 week off.

Some previous phase II clinical studies show effectiveness of capecitabine as monotherapy in patients pretreated with taxane or anthracycline-based chemotherapy [4,5,9,10]. In these studies, capecitabine monotherapy has a response rate of 15-28%, with the median progression-free survival (PFS) of 3.1-4.9 months. Recently, a number of phase III studies also well expound the efficacy and safety of capecitabine in monotherapy or combination therapy.

A large phase III clinical trial has compared the effect and safety of capecitabine used alone or combined with Ixabepilone in 752 cases of patients pretreated with taxane or anthracyclines [11]. Median PFS is 4.2 months in monotherapy of capecitabine, with the response rate of 14%. Though median PFS and response rate are increased in the combination therapy group (5.8 months and 35%), the side effects are also significantly increased. Incidence of grade 3 or 4 sensory neuropathy, malaise and leukopenia are 21%, 9% and 68% in the combination group, and in the monotherapy group, the corresponding rates are 0%, 3% and 11%。

There is another famous phase III clinical trial – the RIBBON-2 study enrolled 462 patients who were pretreated with taxane or anthracyclines [12]. Patients were randomly assigned to monotherapy group (capecitabine) or combination (capecitabine combined with bevacizumab) therapy group. The results show that the response rate was higher in combination group (19.8% vs 9.1%), but there was no improvement for PFS and overall survival (OS).

All clinical data have showed that capecitabine as monotherapy has good safety profile [13]. Hand - foot syndrome is the most common adverse events, which is not life-threatening, and can be well controlled via dose reduction. Capecitabine can also cause mild to moderate gastrointestinal adverse events (such as diarrhea, stomatitis). When the dosage of capecitabine is reduced to 1000 mg/m2 twice a day, grade 3/4 diarrhea incidence will be lower than those of the standard therapy (1250 mg/m2 twice a day) [14]. Importantly, the effective is not compromised [5].

Capecitabine is also used in combination with biological agents such as Herceptin or bevacizumab. But in HER-2 negative patients, it has not obtained the expected effect in the combination therapy with bevacizumab. Therefore, the drug combination of capecitabine with other effective low-toxic drugs is still a good research orientation.

**3. PA-MSHA and its application in breast cancer**

Pseudomonas aeruginosa injection is a new kind of bacteria agent by genetic engineering preparation. The ingredient is “pseudomonas aeruginosa - mannose sensitive hemagglutination” (PA-MSHA) with independent intellectual property rights. Pseudomonas aeruginosa injection was approved by sFDA in 1998. It has been widely used in complementary therapy of a variety of malignancies, including breast cancer. Clinical data showed PA-MSHA can significantly inhibit the growth of tumors and improve life-quality in tumor patients [15,16].

**Action mechanism of** **PA-MSHA**

In 2009, [name] et al (*Fudan University Shanghai Cancer Center*) has performed study on mechanism of pseudomonas aeruginosa injection to treat breast cancer. They have found that Pseudomonas aeruginosa injection has direct targeted killing effects on breast cancer cells (MDA-MB-231HM and MDA-MB-468 cells) in vitro and in vivo. Its unique MSHA fimbria can be specifically bound with mannose molecular of EGFR receptor on the surface of breast cancer cells, so as to block the activation of EGFR receptor and its intracellular signaling molecules (AKT, ERK), thus inhibiting the growth of breast cancer cells and inducing apoptosis; besides, Pseudomonas aeruginosa injectionalso can significantly reduce the levels of the proteins (MMP, E-Cadherin, VEGF) generated by breast cancer cells and associated with tumor metastasis and angiogenesis; The growth of breast cancer in nude mouse models have been effectively controlled, in addition, pulmonary metastasis rate and the number of pulmonary metastases are also significantly lower than the control group. The research outcomes were already published in *the Journal of Cellular Biochemistry* in 2009, and in *Oncogene* in 2010, which provides sufficient theoretical basis for pseudomonas aeruginosa injectionto treat breast cancer in clinic [17,18].

On the other hand, pseudomonas aeruginosa injectionis also found a highly efficient immune activation agent. According to a study in 2008, the MSHA fimbriae of pseudomonas aeruginosa injectioncan fully active the Toll-like receptors (TLR4) on the surface of immune cells [19]; induce mononuclear cells (dendritic cells, macrophages) to differentiation and maturation; further active T lymphocytes (CTL) and the NK cells; induce specific and non-specific anti-tumor immune response; help the body to rebuild tumor immune surveillance and improve the microenvironment of tumor cells [20]. Therefore, pseudomonas aeruginosa injection is a new kind of anti-tumor drug with dual mechanisms: “targeted therapy” and “immune therapy”. Pseudomonas aeruginosa injection-based combination chemotherapy can not only play its strength of targeted therapy, but also can improve the low immunity caused by chemotherapy, thus improving the sensitivity of tumor cells to chemotherapy and reducing the side effects of chemotherapy.

**Application of pseudomonas aeruginosa injection in breast cancer therapy**

Most of the researches on pseudomonas aeruginosa injection are about its application in neoadjuvant chemotherapy. In a single-center clinical study conducted by *Tianjin Medical University Cancer Hospital* in 2009, 40 women with locally advanced breast cancer (LABC) (II~III) were randomly divided into two groups. The experimental group were given TE chemotherapy combined with subcutaneous injection of pseudomonas aeruginosa injection, while in control group, only TE chemotherapy was adopted. Both of the groups were given radical mastectomy or breast-conserving surgery after 4 months of chemotherapy. The results show that the total response rate (RR) was 85% in experimental group, significantly higher than the control group by 60% (P<0.05); Pathologic complete response rate (pCR) was 30% in the experimental group, higher than the control group by 10%. For the patients’ physical condition, after the treatment, Karnofsky score in experimental group was obviously higher than the baseline and also higher than that of the control group (P<0.01). Serum IFN-γ and IL-2 were increased while serum IL-4 and IL-10 were reduced in the experimental group after the treatment, the indexes before and after the treatment were all significantly different (P<0.05); after the treatment, the above indexes are of statistically significant differences between the experimental group and the control group (P<0.01). For tumor cell apoptosis and metastasis associated protein, serum Caspase-3 was raised while serum VEGF, MMP-2 and MMP-9 were reduced in the experimental group after treatment (P<0.05). Safety evaluation showed that no severe extramedullary adverse reaction and the acute cardiac toxicity were observed in both the experimental group and control group [21].

In a single-center clinical study conducted by *The Second Xiangya Hospital of Central South University* in 2009, 60 women with LABC (T2~T4) were randomly divided into two groups. The experimental group were given TAC chemotherapy combined with subcutaneous injection of pseudomonas aeruginosa injection for 21 days (once every day); While in control group, only TAC chemotherapy was adopted, the patients were given chemotherapy for 2~4 cycles based on the curative effect, and then given surgery. The research results showed that after 2 cycles of chemotherapy, total RR was 76.7% in the experimental group, which was significantly higher than that of the control group. And after chemotherapy of 3~4 cycles, there were still significant differences. For the patients’ physical condition, Karnofsky score showed no significant difference before and after treatment in the experimental group, but in the control group, Karnofsky score was obviously reduced. For chemotherapy toxicity, the most common toxic effects in the two groups were nausea, vomiting, bone marrow suppression and alopecia. Whether the incidences or the degrees of toxic reaction were significantly decreased in the experimental group compared with the control group [22].

Breast cancer is a heterogeneous disease, where different subtypes have different sensitivities to chemotherapy as well as different prognosis. Patients with HER-2 receptor negative breast cancer, especially with Luminal A type breast cancer of HER-2 negative and ER positive, pCR rate that the neoadjuvant chemotherapy can achieve is lowest; Even for patients with three negative breast cancer, whose pCR rate is relatively high, the long-term prognosis is not ideal. For example, in the neoadjuvant chemotherapy study (Paclitaxel + Carboplatin (PCb), every week) of *Fudan University Shanghai Cancer Center*, pCR rates were higher in patients with ER negative, PR negative, HER-2 negative or three negative, the corresponding rates were 32.6%, 30.6%, 33.3% and 33.3%, while in patients with ER positive or Luminal A type (ER positive, HER-2 negative) breast cancer, the pCR rates were lower, of only 9.7% and 8.3%. Therefore, the patients must be give corresponding treatments according to the different types of biological behaviors [23]. In general, for breast cancer patients with HER-2 receptor negative, the poor effect of the new adjuvant chemotherapy and Herceptin unavailable to use, further restrict the clinical treatment and therapeutic effect on such patients. So HER-2 receptor negative breast cancer is the difficulty in the treatment, which urgently needs new therapies.

On the basis of these encouraging preclinical and clinical data, we performed a single arm, phase II clinical trial using PA-MSHA combined with capecitabine as salvage treatment for Her-2–negative MBC patients pretreated with anthracyclines and taxanes.

**II.Study design**

This phase II, single centre, single arm, open-label study is designed to evaluate the efficacy and safety of capecitabine plus PA-MSHA in subjects with Her-2 negative metastatic breast cancer pretreated with anthracycline and taxane.

**III. Inclusion and exclusion criteria**

**1. Inclusion criteria**

1) Women aged between 18 and 70 years；

2)Histologically confirmed Her-2–negative MBC；

3) Not suitable for local treatment;

4) Pretreated with antracyclene and taxane；

5)Prior capecitabine-containing therapy was permitted if the disease had responded to the drug previously and progressed at least 4 months after drug discontinuation；

6)ECOG performance status of no more than 2；

7) Adequate organ function；

8) Having the following laboratory values; WBC≥4×109/L；Hb≥90 g/L；plt≥100×109/L；

9) Written informed consent should be obtained before study procedure.

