**2. Exclusion criteria**

1. Pregnant or lactating females；
2. Prior history of malignancies, other than breast cancer；
3. Having participated in a prior investigational study within 1 months prior to Day 1 dosing；
4. Uncontrolled intercurrent illness；
5. Known sensitivity or allergy to PA-MSHA；
6. Unwilling or unable to comply the protocol；
7. Any other condition that investigator think the subject is not suitable for the study.

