**XII. Sample size**

It is expected that the PFS will be prolonged from 4.2 months with monotherapy of Xeloda to 5.7 months after combined with pseudomonas aeruginosa injection. So according to a=0.05 and power of 85%, the needed sample size is 88 cases; 96 patients were required in consideration of 10 % expulsion rate.

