**4. Statistical expression**

Bilateral inspection is adopted generally, P less than or equal to 0.05 will be considered a statistically significant discrimination.

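### Apart from prior capecitabine and recent trial therapy, entry requires only exposure to an anthracycline and a taxane, not progression, while single-arm PFS is planned against a benchmark trial in progressing disease

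*Protocol*

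**What the plan says.** The Protocol summary describes a "Phase II, single arm, single center clinical trial". Section XII plans the primary endpoint against a fixed figure: "PFS will be prolonged from 4.2 months with monotherapy of Xeloda to 5.7 months". That section names no source. The only place where 4.2 months appears as a capecitabine result is section I.2, for the monotherapy arm of the phase III trial of capecitabine with or without ixabepilone. The title of that trial in the reference list (item 11) says that the disease was progressing after anthracycline and taxane treatment.

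On entry, section III.1 item 4 reads "Pretreated with antracyclene and taxane" and goes no further. Two narrower rules stand beside it:
- Section III.1 item 5 allows prior capecitabine only if the disease responded and then progressed at least 4 months after the drug was stopped.
- Section III.2 item 3 excludes "Having participated in a prior investigational study within 1 months prior to Day 1 dosing".

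The end of the Introduction describes the regimen "as salvage treatment for Her-2–negative MBC patients pretreated with anthracyclines and taxanes". Section VI.1 collects extent of cancer, medical history and prior anti-cancer treatment at screening. For PA-MSHA itself, only known sensitivity or allergy excludes (section III.2 item 5), although section I.3 says of the marketed product: "It has been widely used in complementary therapy of a variety of malignancies, including breast cancer".

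**The concern.** Salvage treatment implies that the previous treatment has failed. The entry criteria do not enforce this. A woman with metastatic disease who is stable or responding after a taxane-based regimen meets item 4 as fully as one who has progressed on it.

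In a randomised trial such patients would fall in both arms. Here there is no concurrent arm. If part of the cohort enters with disease still controlled by the last regimen, that control is counted in the PFS of the combination, and shrinkage still under way can be counted as response. The comparison with 4.2 months would then partly reflect a difference in populations. No analysis can separate the two unless progression status at entry is known, and the screening list does not name it.

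A smaller matter is that a woman who has taken, or is taking, PA-MSHA in routine care may enrol. Her screening immune values may then not be drug-free baselines.

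**Working it through.** **1. The planned comparison.** The inputs are medians of 4.2 and 5.7 months and "according to a=0.05 and power of 85" percent (section XII), two-sided because "Bilateral inspection is adopted generally" (section XIV.4). No method is stated. A single-arm exponential test on the median scale gives

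d = (1.960 × 4.2 + 1.036 × 5.7)² / (5.7 − 4.2)² = 88.9,

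that is 89, against the stated 88. The sample size therefore fits a comparison of one cohort with a fixed 4.2 months. The targeted gain is 5.7 − 4.2 = 1.5 months. This point does not dispute the sample size.

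**2. What entry requires, by last therapy.**

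| Last therapy before entry | Progression required? | Interval required? |
|---|---|---|
| Capecitabine-containing | Yes, after response | Progression at least 4 months after stopping |
| Given in an investigational study | No | 1 month |
| Anthracycline, taxane, other routine chemotherapy | No | No |
| Hormonal therapy | No | No (barred during the study, section VII.1) |
| PA-MSHA in routine care | No | No |

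The gap lies in the last three rows.

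**3. How far it could move the median.** The documents give neither the share f entering with controlled disease nor the median PFS m of those patients. Both are assumptions. Assume also that PA-MSHA has no effect, that PFS is exponential in each subgroup, and that patients in progression have a median of 4.2 months. The median t of the whole cohort solves

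(1 − f) × 2^(−t/4.2) + f × 2^(−t/m) = 0.5.

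Check for f = 0.3, m = 12, t = 5.51: 0.7 × 2^(−5.51/4.2) = 0.282 and 0.3 × 2^(−5.51/12) = 0.218, which sum to 0.500.

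| f | m = 7 | m = 9 | m = 12 |
|---|---|---|---|
| 10% | 4.40 | 4.49 | 4.57 |
| 20% | 4.62 | 4.81 | 5.01 |
| 30% | 4.85 | 5.17 | 5.51 |

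As a share of the 1.5-month gain, (t − 4.2)/1.5, the rows are 13-25%, 28-54% and 43-88%.

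**4. A second model.** Take 88 patients, all with events, exponential PFS with a true median of 4.2 months, and c extra months of carried-over control in a share f. The simulated chance of wrongly exceeding 4.2 months in the upper tail of a two-sided 0.05 test is:

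| f | c (months) | False-positive chance | Observed median |
|---|---|---|---|
| 0 | – | 2.6% | 4.2 |
| 10% | 2 | 4.6% | 4.4 |
| 20% | 2 | 8.1% | 4.7 |
| 30% | 3 | 25.1% | 5.3 |

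Both models show the same pattern: a small effect at a 10% share and a large one at 30%.

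**The case against.** The strongest reply is that few such patients would enrol.
- Women relapsing after adjuvant anthracycline and taxane have in effect progressed, and section I.1 says that adjuvant use is widening.
- The stated salvage purpose argues against maintenance use.
- The investigator may exclude anyone unsuitable (section III.2 item 7).
- Blood-count and organ-function limits (section III.1 items 7 and 8) make entry straight after chemotherapy less likely.

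All of this stands, and it confines the gap mainly to patients already treated for metastatic disease. It does not close the gap. Discretion is not a criterion, and neither it nor the laboratory limits document progression.

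A second reply is that other entry rules may shorten PFS: ECOG 2 is allowed and prior lines are not limited. This also stands. The net bias against 4.2 months is therefore unknown. Only the carry-over component has a known direction, in favour of the combination.

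A third reply is that section VI.1 already records prior treatment. It does, but as data to collect and not as a condition of entry, and progression status is not listed.

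A reader might infer more than the text supports:
- That eligibility contains no progression or interval rule at all. The capecitabine and investigational-study rules show otherwise.
- That prior PA-MSHA use undermines the primary result. No document says how many candidates have used it, and the Protocol summary classes the immune index as exploratory.
- That a fixed washout should cover all earlier treatment, including radiotherapy. That would sit awkwardly with section VII.3, which allows palliative radiotherapy for pain on study.

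**Conclusion.** The point holds in a limited form. For last therapies other than capecitabine, no criterion requires progression, and an interval is set only after an investigational study. The figure used for comparison comes from a trial described by its title as enrolling progressing disease. Followed exactly as written, the protocol can credit carried-over control to the combination.

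The size cannot be fixed from the documents. Under no drug effect and exponential PFS, a 10-30% share with a median of 7-12 months gives an observed median of about 4.4-5.5 months, or 13-88% of the targeted gain. The low end matters little and the high end would come close to the 5.7-month target. Nothing in the documents shows which end is nearer. The match of the 4.2 months to the ixabepilone trial rests on section I.2, and the description of its population rests on the title alone, because section I.2 says only that patients were pretreated.

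The change should be made because it is cheap and the single-arm analysis cannot repair the problem later without the data. Prior PA-MSHA use is a minor addition.

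**What to change.** Reword section III.1 item 4, and the same item in the Protocol summary, to require documented progression or relapse on or after the most recent systemic therapy, following prior anthracycline and taxane. The word relapse keeps patients who recur after adjuvant treatment eligible. Item 5 and the investigational-study rule can stay as they are.

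For patients already enrolled, record progression status at entry from the source records, and report PFS and ORR in those with documented progression beside the full result.

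As a minor addition, identify prior or current PA-MSHA use within the treatment history that section VI.1 already collects, and report the immune index and PFS without those patients as a sensitivity analysis.

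The cost is a short eligibility amendment and one more data item at screening. Accrual may slow slightly, and the subset with documented progression will be somewhat smaller than the full cohort, so its estimates will be less precise.
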